### Objectives and hypothesis {7}

#### Primary research question

Does a modified adult chronic condition self-management program plus standard care improve therapy adherence in adolescents aged 15–18 years with a chronic condition compared to standard care only?

The *primary objective of this stud*y is to investigate the effectiveness via adherence of a modified adult chronic condition self-management support program in an adolescent population with a chronic condition within a tertiary pediatric hospital setting, compared to those receiving routine care services in the same setting using standardized markers of improvement in control of their chronic illness.

The *secondary objectives* include the use of routinely collected data on the number of unplanned or unscheduled health care or emergency department visits, together with questionnaire measures of quality of life, self-efficacy, time management, health-related distress, and feasibility and acceptability of the program to further refine its delivery under clinical conditions.

*Study hypothesis* to be tested is that a modified adult-focused, generic chronic condition self-management support program provided to adolescents with a chronic condition who are in the active phase of transition to adult services would:Be more effective than standard usual care in achieving adherence to chronic condition management as measured by quantitative condition-specific validated markers of improvement in illness control as described in Table 1.Be more effective than standard care in improving more global quality of life, self-efficacy, time management, and in reducing health-related distress as described in Table 2.

**Table 1 Tab1:** Markers of illness control

Chronic condition	Measures of illness control	Definition of improvement^*^
Cystic fibrosis	▪ FEV1	FEV1% of predicted increased by ≥ 10%
Type 1 diabetes mellitus	▪ HbA1c	Absolute decrease in HbA1C by ≥ 1% (e.g., 9% reducing to 8%)
Inflammatory bowel disease	▪ Weight	Absolute increase in weight by ≥ 5%
Chronic kidney disease	▪ GFR	Absolute increase in GFR by ≥ 5%
Asthma	▪ FEV1	FEV1 % of predicted increased by ≥ 10%
Epilepsy	▪ Number of seizures	Based on individual and type of seizure as negotiated with treating Neurologist.

Abbreviations measures of illness control: *FEV1 (%)* forced expiratory volume in 1 s, *HbA1c* glycosylated hemoglobin (mmol/mol), *GFR* glomerular filtration rate (mL/min)

Weight (kilograms)

^*^Sustained improvement in measure of disease control over a 12-month period from baseline

**Table 2 Tab2:** Schedule of enrolments, interventions, and assessments

Procedure												
**Measure**	**Baseline**		**3 months**		**6 months**		**9 months**		**12 months**		**18 months**	
	**I**	**C**	**I**	**C**	**I**	**C**	**I**	**C**	**I**	**C**	**I**	**C**
Informed consent	**X**	**X**										
Demographic data collection	**X**	**X**										
Measures of illness control	**X**	**X**	**X**		**X**	**X**		**X**	**X**	**X**		**X**
Unplanned hospital visits	**X**	**X**	**X**		**X**	**X**		**X**	**X**	**X**		**X**
Questionnaires	**X**	**X**	**X**			**X**		**X**	**X**			**X**
Partners in Health (PIH) Scale	**X**	**X**	**X**		**X**	**X**		**X**	**X**	**X**		**X**
Feasibility and Acceptability Questionnaire (FAQ)									**X**			**X**
Flinders Program delivery	**X**		**X**		**X**	**X**	**X**	**X**	**X**	**X**		**X**
Booster session					**X**					**X**		

***I*** Intervention (Flinders Program plus usual care), ***C*** Control (waitlist plus usual care)

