### Eligibility criteria {10}

To be eligible for the trial, adolescents must meet the following criteria: (1) aged between 15 and 18 years; (2) have a chronic physical condition needing regular health care and requiring the development of self-management skills; (3) be identified by their treatment team as having unsatisfactory control of this condition. As we are an intervention service, at recruitment all our sample will have unsatisfactory control of their chronic condition based on the clinical judgment of their treating team and/or markers of illness control which is an inclusion criterion; (4) they must not have previously participated in a self-management program in the last 2 years. The rational for the choice of age criterion was based on the developmental stage of the adolescent. From middle adolescence (15–16 years) to late adolescence (17–19 years), young people are at a developmental stage where, from a neurocognitive perspective, they are better able to articulate and comprehend the information provided as their transition from pediatric to adult services is planned. From a developmental perspective, cognitively in early adolescence (12–14 years), it is challenging for an adolescent to conceptually understand and process the information provided in the Flinders Program™ as evident from our past clinical experience [36].

Eligible participants will be provided with a patient information sheet (PIS) and a consent form as identified by their primary treating team and then introduced to the research team. Parents/carers will also be provided with a parent information sheet describing the full details of the study. Ideally the consent will be provided face to face on the day. If the consent is not returned within 7 days, follow-up phone contact with the young person will be made by the research nurse to discuss consent.

The participant exclusion criteria include the following: (1) any adolescents who lack competence in English and are unable to understand and consent to participation in the study; (2) adolescents with an intellectual disability precluding independent self-management; (3) adolescents with any chronic condition with no routinely measurable quantitative condition-specific validated markers of illness control that can be used to identify clinically meaningful endpoints for example some metabolic disorders. The ineligible adolescents in this group will however be included in the self-management support clinic.

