## Assignment of interventions: allocation

### Sequence generation {16a}

Following formal consent, the participants will be randomized. Successively, baseline data collection and measures of illness control will be collected for both the control and intervention groups. Randomization will be stratified by disease condition (diabetes, CF, renal, inflammatory bowel disease, other) and will use permuted blocks to maintain balance.

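### The kidney response marker is GFR in mL/min, not indexed to body size, so growth in 15–18 year-olds can supply part of the 5% rise that counts as improvement

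*Protocol article*

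**What the plan says.** Table 1 (Objectives and hypothesis {7}) defines response for the binary primary outcome, one marker per condition. For chronic kidney disease the criterion is "Absolute increase in GFR by ≥ 5"%. The abbreviation line beneath the table gives the unit as "glomerular filtration rate (mL/min"). No other section of the article mentions indexing GFR to body surface area.

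For cystic fibrosis the criterion is "FEV1% of predicted increased by ≥ 10"%, and the asthma row also uses per cent of predicted, so both lung rows are normalised for body size. The table footnote requires "Sustained improvement in measure of disease control over a 12-month period from baseline". Participants are "aged between 15 and 18 years" (Eligibility criteria {10}). Renal disease is one of the five randomisation strata: "diabetes, CF, renal, inflammatory bowel disease, other" (Sequence generation {16a}).

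**The concern.** GFR in mL/min is a whole-body quantity. If kidney function per unit of body size stays the same while the body grows, GFR in mL/min rises. Some participants aged 15–18 will still be growing over a 12-month window, and the threshold is a small percentage rise. Part of that rise can therefore come from growth and say nothing about illness control or adherence.

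The same table removes body size from the lung marker, so the lack of adjustment for GFR stands out. At stake is the response rate among renal participants. If growth turns some true non-responders into responders in both arms, the control rate rises above its true level and the difference between arms shrinks. The sample size section plans on 15% or less under usual care and 80% power with 27 per group, which leaves little slack. The point concerns which quantity is measured. It is separate from whether 5% is a sensible threshold, and from the weight criterion for inflammatory bowel disease.

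**Working it through.** **1. The plan's own figure.** Sample size {14} gives 15% under usual care, a 35-point difference (so 50%), two-sided 5%, 80% power and a chi-square test. The pooled-variance formula without continuity correction gives 27 per arm, with power 80.2% at 27. The stated figure reproduces.

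**2. How growth enters.** Two assumptions, neither in the documents: body surface area (BSA) is proportional to √(height × weight), and un-indexed GFR equals indexed GFR × BSA up to a constant. With BSA growth g, the indexed rise needed to reach the 5% threshold is 1.05/(1+g) − 1:

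| BSA growth over the year | Indexed rise needed |
|---|---|
| 0% | 5.00% |
| 1% | 3.96% |
| 2% | 2.94% |
| 3% | 1.94% |
| 4% | 0.96% |

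**3. When growth alone reaches 5%.** This needs (1+h)(1+w) = 1.05² = 1.1025, where h and w are the fractional gains in height and weight:

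| Height gain | Weight gain needed |
|---|---|
| 0% | 10.25% |
| 1% | 9.2% |
| 2% | 8.1% |
| 3% | 7.0% |

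More modest growth gives part of it. Weight +5% with height +1% gives √(1.05 × 1.01) − 1 = 3.0%. No growth gives 0%.

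**4. Effect on false response among renal participants.** Assumptions: measurement SD 5% on the log scale at baseline and each visit, linear growth, constant indexed GFR, 400,000 simulated participants. Share at least 5% above baseline:

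| Rule | g = 0 | g = 2% | g = 5% |
|---|---|---|---|
| Months 3, 6 and 12 all qualify | 7.1% | 9.9% | 14.9% |
| Months 6 and 12 both qualify | 11.7% | 16.8% | 26.1% |

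The part due to growth is 2.8 to 7.8 points under the first rule and 5.1 to 14.4 under the second. Both rules are shown because Table 2 has no 3-month illness-control measure for controls, while sections {12} and {18a} list one.

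**5. Effect on the whole sample.** The renal share is not stated; 10% to 30% is assumed. Smallest: 2.8 × 0.10 = 0.3 points. Largest: 14.4 × 0.30 = 4.3 points.

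**6. Effect on power.** Let s be the renal share and f the extra fraction of true renal non-responders scored as improved, equal in both arms. The control rate becomes 0.15 + 0.85sf and the intervention rate 0.50 + 0.50sf. Power at 27 per arm:

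| s | f | Control | Intervention | Power |
|---|---|---|---|---|
| – | 0 | 15.0% | 50.0% | 80.2% |
| 10% | 2.8% | 15.2% | 50.1% | 79.8% |
| 20% | 5.1% | 15.9% | 50.5% | 78.8% |
| 30% | 14.4% | 18.7% | 52.2% | 74% |

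**7. If indexed GFR is falling.** With an assumed 5% yearly decline and the months 6 and 12 rule, false response is roughly 4%, 6% and 11% for growth of 0, 2 and 5%. The part due to growth is then about 2 to 8 points instead of 5 to 14.

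**The case against.** The strongest reply is that the unit sits in an abbreviation line and not in the criterion itself. That line is unreliable elsewhere: it lists "glycosylated hemoglobin (mmol/mol") although the HbA1c criterion is in percentage points. Markers are extracted from the electronic medical record, and the value there may already be indexed. The defect would then be an incomplete unit in a legend. This stands as a limit on certainty, but it does not remove the point: mL/min is the only definition the article gives, and a reader who follows it would use the un-indexed quantity.

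The second reply is that every input to the size estimate is assumed: growth, noise, renal share and constant indexed GFR. That is correct. The protocol itself expects deterioration without intervention (Trial design {8}), and a decline makes the growth effect smaller. Measurement noise alone already gives 7–12% false response in the simulation, more than 2% growth adds.

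The third reply is that the comparison is not biased towards either arm. This also stands. Randomisation is stratified with a renal stratum, so growth should be similar in both arms.

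**Conclusion.** The point holds as a defect in a stated unit, with a modest effect. As written, the kidney marker is not adjusted for body size, and growth can supply part of the 5% rise. BSA growth of 1–4% lowers the indexed improvement needed to about 4.0–1.0%.

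A reader might infer that growth alone routinely turns renal participants into responders. The documents do not support that: they give no growth rates, the full 5% needs about 7–10% weight gain in a year, and participants who have stopped growing are unaffected. A reader might also infer bias in favour of the programme. That is not supported either, because the expected effect is the same in both arms: a somewhat higher response rate and a diluted difference.

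Overall false response rises by about 0.3 to 4 points, assuming 2–5% growth, 5% measurement SD, constant indexed GFR and a 10–30% renal share, and by less if indexed GFR is declining. Power falls from 80.2% to between 79.8% and 74%, the low end needing the most unfavourable value of every input. The correction is still worth making, because it concerns a component of the primary outcome and costs almost nothing.

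**What to change.** In Table 1 and its legend, define the renal marker as GFR indexed to body surface area (mL/min/1.73 m²), obtained by the same method at baseline and at every follow-up. State that the existing 5% is a relative change from baseline, since the present wording joins an absolute increase to a percentage. If the value extracted from the medical record is already indexed, correct the legend unit to say so.

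The cost is one line in Table 1 and one field on the extraction form. Height, weight and creatinine, or a reported indexed GFR, should already be in the record, though the documents do not confirm this. No visit or participant is added.

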### Trial design {8}

This is a pragmatic, two-site, two-arm, parallel, longitudinal randomized controlled trial, using both quantitative and qualitative research methods. Participants are allocated at a ratio 1:1 to the intervention or usual care using a computer-generated random list. An RCT design was chosen for this study due to its accepted applicability in assessing the effects of new healthcare interventions such as a self-management program [37, 38]. This study design has been shown to demonstrate sound methodological evidence [39], and allows for a comparison group at each time period and for analysis between each cluster [37, 40]. The study protocol received approval by The Sydney Children’s Hospitals Network Human Research Ethics Committee, Sydney, Australia. The study protocol has been developed based on the Standard Protocol Items: Recommendations for Interventional Trials (SPIRIT) guidelines Schulz and Grimes [41] (see Additional File 1). Figure 2 demonstrates the flowchart of the study design.

This protocol describes an RCT to demonstrate the efficacy of the Flinders Program™ in adolescents. Following randomization, participants in the intervention group will receive a 12-month nurse-led modified version of the Flinders Program™ plus standard care, while participants in the waitlist control group will receive standard care for 6 months before crossing over to the intervention group until all participants are exposed to the program as demonstrated in the study design diagram in Fig. 1. Given that the data available suggests continuing deterioration without intervention is expected, we consider it ethically responsible to offer the intervention to both participant groups.

**Fig. 1 Fig1:**
[figure not shown]
CONSORT (Consolidated Standards of Reporting Trials) flowchart for the self-management randomized controlled trial

The study design will include a baseline collection period, followed by sequential, individual randomization to control or intervention. The intervention group and control group will be continually recruited and exposed to the intervention plus standard care and/or standard care with baseline and follow-up observations collected (see “Participant timeline {13}”) until target numbers are achieved (see sample size {14}). All participants will be asked to sign informed consent before the commencement of the study.

This is a pragmatic trial for the following reasons:Our systematic review published in the Journal of Advanced Nursing (2021), provides evidence that self-management programs are effective for adolescents. We have been using the Flinders Program™ clinically for over 5 years with success in demonstrated effectiveness in self-management capacity. What is less well understood is how effective self-management programs remain over time, given the rapid bio-neuro-psychosocial development during adolescence. This study has the capacity to demonstrate duration of effect with 12-month follow-up planned.Given the challenge of recruiting and retaining adolescents in health service research from the clinical experience of the research team and the clear clinical need to intervene [36], the combination of stepped intervention with assessment of duration of effect and guidance on booster sessions appears the more appropriate methodological option.

#### Study design diagram

Figure 1 shows the CONSORT (Consolidated Standards of Reporting Trials) flowchart for the self-management randomized controlled trial.

## Methods: participants, interventions and outcomes

### Study setting {9}

This study is being conducted within specialist clinics in two large tertiary pediatric university teaching hospital across the two campuses of the Sydney Children’s Hospital Network (SCHN) in Sydney, Australia. Participants will be recruited from The Children’s Hospital at Westmead and Sydney Children’s Hospital Randwick. The SCHN is the largest tertiary pediatric health care entity in Australia, providing world-class pediatric healthcare and research. In the 2019–2020 financial year, the SCHN provided care for over 153,000 children and young people, totalling over 50,000 hospital admissions and servicing different geographical areas of the state of New South Wales, Australia [42]. The population to be studied is adolescents aged 15–18 years of age with a chronic condition who have been identified by their treating team as requiring the development of self-management skills to effectively manage the challenges associated with their chronic illness.

### Eligibility criteria {10}

To be eligible for the trial, adolescents must meet the following criteria: (1) aged between 15 and 18 years; (2) have a chronic physical condition needing regular health care and requiring the development of self-management skills; (3) be identified by their treatment team as having unsatisfactory control of this condition. As we are an intervention service, at recruitment all our sample will have unsatisfactory control of their chronic condition based on the clinical judgment of their treating team and/or markers of illness control which is an inclusion criterion; (4) they must not have previously participated in a self-management program in the last 2 years. The rational for the choice of age criterion was based on the developmental stage of the adolescent. From middle adolescence (15–16 years) to late adolescence (17–19 years), young people are at a developmental stage where, from a neurocognitive perspective, they are better able to articulate and comprehend the information provided as their transition from pediatric to adult services is planned. From a developmental perspective, cognitively in early adolescence (12–14 years), it is challenging for an adolescent to conceptually understand and process the information provided in the Flinders Program™ as evident from our past clinical experience [36].

Eligible participants will be provided with a patient information sheet (PIS) and a consent form as identified by their primary treating team and then introduced to the research team. Parents/carers will also be provided with a parent information sheet describing the full details of the study. Ideally the consent will be provided face to face on the day. If the consent is not returned within 7 days, follow-up phone contact with the young person will be made by the research nurse to discuss consent.

The participant exclusion criteria include the following: (1) any adolescents who lack competence in English and are unable to understand and consent to participation in the study; (2) adolescents with an intellectual disability precluding independent self-management; (3) adolescents with any chronic condition with no routinely measurable quantitative condition-specific validated markers of illness control that can be used to identify clinically meaningful endpoints for example some metabolic disorders. The ineligible adolescents in this group will however be included in the self-management support clinic.

### Who will take informed consent? {26a}

The principal investigator retains the overall responsibility for ensuring that consent has been obtained from participants in the correct manner. The principal investigator may delegate this responsibility to a member of the research team with the appropriate training, experience, and knowledge to explain fully to potential research participants the implications of participating in the trial. Trial data will be collected from potential trial participants by a member of the research team via telehealth, in person or by phone or email if other methods are unobtainable. Following the confirmation of the participant eligibility and the participant has had time to review the study information provided, consent will be sought. Informed consent (see Additional File 2), where possible, will be collected in person by a member of the research team prior to the collection of baseline data. All participants will be assigned a study identification code linked to their personal information. All trial data will be recorded and stored in a separate password-protected computer within the Department of Adolescent Medicine at The Children’s Hospital at Westmead and accessible only by the primary research investigators (JG, KS) and any research staff associated with the study. Signed consent forms, questionnaires, and other paper data including the master list linking the personal information of participants and personal ID numbers will be secured in a separate locked cabinet in the Department of Adolescent Medicine and accessible only by the primary research investigators.

### Additional consent provisions for collection and use of participant data and biological specimens {26b}

This trial does not involve collection of biological specimens for storage.

The Australian National Health and Medical Research Council (NHMRC) statement identifies that young people can consent to participate in research without additional consent from parent(s) and/or guardian(s) where the young person has developed the capacity and maturity to understand and consent to participation which involves no more than low risk and where the research aims to benefit the young person (NHMRC, 2007). Adolescents will be able to provide their own consent to be part of the study for the following reasons.In Australia, adolescents can have their own Medicare card and seek independent health advice from 15 years and have access to their own My Health Record from 14 years of age. At 16 years, adolescents are able to consent to all medical procedures except sterilization or gender reassignment surgery. A “mature minor” aged 14–16 years as defined by NSW laws can independently consent to or refuse medical treatment if they have enough intelligence, competence, and a full understanding of the medical treatment proposed [43]. This is referred to as “Gillick Competence.” The Flinders Program is delivered individually without parents present and is unlikely to be effective if the adolescent is unwilling to be part of the program; therefore, the young person’s individual consent is requested in line with Gillick competence guidelines.The program is about adolescents moving towards autonomy in their illness management and being able to consent, rather than just assent, is an important signal about emerging autonomy.If the young person is interested in the research program but the parents may not be interested due to the impact on work commitments, or are time poor, we can deliver the program digitally and thus at no cost or inconvenience to the parent.Some young people are already attending medical care independently often with longstanding relationships with their primary care team.The self-management program is in no way involved in treatment change or scheduling. It works by supporting the young person to manage the agreed treatment plan as determined by their treating team.

Ethics approval has been granted for young people aged 15–18 years to provide their own consent rather than parent/guardian consent for the reasons listed above. Each participant will be asked to sign a consent form to participate in the study. It is important for the study that the young person has consented to working with the health professional and developing increased capacity to make independent decisions as they transition to adult services. The young person’s capacity to consent will be judged with advice from the treating teams who have had a longstanding therapeutic relationship with the young person. In addition, Gillick Competence will be determined by the research team who have extensive experience and expertise in working with adolescents and will also be able to assess the young person’s competency and capacity to consent.

